### Data collection

Monthly patient record reviews of patients 70 years or older will be the main source of data. During 11 months, research nurses will review approximately 10 records per ward per month (20 per hospital), using both nursing and medical records. If a ward provides the research nurse with more than 10 records fitting the inclusion criteria, the nurse will take a random sample from the available records. All record reviews will take place within the same week of the month, using records of patients still in hospital or discharged during the previous week. From these records, data concerning provided delirium care will be gathered, which will offer the following information about the implementation of the delirium aspect of the Frail Elderly Project:

1. Detection of risk for delirium, as well as screening for falls, malnutrition, and physical impairment. The Frail Elderly Project has provided hospitals with screening instruments to assess these risks (Additional file 1). Alternative instruments that are used by hospitals are the Groningen Frailty Indicator [32] and the Identification of Seniors At Risk or ISAR [33].

2. Detection of delirium by nurses using the Delirium Observation Screening scale [34,35] (Table 1).

3. Diagnosis of delirium by physicians.

4. Prevention of delirium by nursing or medical interventions targeting common reversible causes of delirium.

5. Treatment of delirium by starting nursing or medical interventions targeting common reversible causes of delirium or by prescribing medication.

**Table 1 T1:** Delirium Observation Screening scale [34,35]

	The patient:	Never	Sometimes or always
1	Dozes during conversation or activities	0 points	1 point

2	Is easily distracted by stimuli from the environment	0 points	1 point

3	Maintains attention to conversation or action	1 point	0 points

4	Does not finish questions or answers	0 points	1 point

5	Gives answers which do not fit the question	0 points	1 point

6	Reacts slowly to instructions	0 points	1 point

7	Thinks to be somewhere else	0 points	1 point

8	Knows which part of the day it is	1 point	0 points

9	Remembers recent events	1 point	0 points

10	Is picking, disorderly, restless	0 points	1 point

11	Pulls IV tubes, feeding tubes, catheters etc.	0 points	1 point

12	Gets easily or suddenly emotional (frightened, angry, irritated)	0 points	1 point

13	Sees persons/things as somebody/something else	0 points	1 point

For each of three daily shifts the total score is calculated; the total score per shift is a minimum of 0 and a maximum of 13; the total score for a day is a minimum 0 and a maximum of 39. The DOS scale final score is calculated by dividing the total score for the day by 3; the DOS final score is between 0 and 13

The cut-off point is 3; a DOS scale final score of 3 or more indicates a delirium

In addition to data regarding the implementation of the Frail Elderly Project, data regarding the demographic and clinical characteristics of the patients will be gathered.

The record reviews will be carried out by specially trained nurses who have previous experience with reviewing records. An online registration tool will provide these nurses with the means to collect data in the various hospitals. The research nurses will be blinded for the trial condition of the hospitals and are not employed by the hospital where they are conducting the record reviews. Because the e-learning will be used by nurses of the wards participating in the study, the hospitals and wards cannot be blinded to the trial condition.

Besides data from the patient record reviews, data regarding the use of the e-learning course will be gathered. These data include characteristics of the nurses that are given access to the course, such as age, gender, and educational level. Whether the nurses use the course and if so, how often and for how long, will be registered with the web-based course itself. All users will be obligated to complete a delirium knowledge test before and after using the e-learning. These tests consist of randomly selected questions from large question databases. After successfully completing the e-learning and knowledge tests, users will be asked to complete a short evaluation of the course. This evaluation contains five questions regarding the use of the course and the attitude and intention of the user concerning improving delirium care.

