### Study design

The study will be conducted using a stepped wedge cluster randomised trial design. The defining feature of this design is that the intervention will be introduced to all clusters -- or in this instance, hospitals -- in a sequential order [25,30,31]. At the start of the study in May 2011, no hospital will have access to the intervention, while at the end in March 2012 all hospitals will have been given access. This offers an advantage over parallel trials, in which certain hospitals would not receive the intervention. The e-learning course is expected to do more good than harm, making it unethical to withhold the intervention from participating hospitals [25,31].

After every monthly data collection moment, one or two new hospitals will receive access to the intervention, as illustrated in Figure 1. The start date at which each hospital is given access to the e-learning course will be randomly assigned, using simple or unrestricted randomisation. Hospitals will each be informed of the start date of the intervention prior to the start of the trial. After a period of 11 months, all 18 hospitals will have received the intervention, and the stepped wedge design will have resulted in gathered data from all hospitals for both the control and the intervention group. This offers an important methodological advantage: each hospital acts as its own control, thereby reducing contamination bias [31].

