### Research population

Records of patients admitted to the participating wards will be included in the study if the patient is 70 years or older and if the length of stay at the time of the record review is at least 24 hours. Only records of patients still in hospital at the time of the record review and patients discharged in the previous week will be included. A total of approximately 3,960 patient records will be reviewed in the course of the study.

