### Outcomes and data analysis

In the Frail Elderly Project hospitals are advised to screen all elderly patients directly after admission for the risk of developing or the presence of delirium, falls, malnutrition, or physical impairment. The e-learning course educates nurses on screening for delirium. The percentage of elderly patients that are indeed screened for the risk of delirium is the primary outcome of this study. Secondary outcome measures include: the percentage of elderly patients with an increased risk of delirium that are observed with the Delirium Observation Screening scale; the percentage of elderly patients with (an increased risk of) delirium that receive care aimed to prevent or treat delirium; and the percentage of elderly patients that are diagnosed with delirium. Covariates that will be used in the analysis are: age, gender, living situation, comorbidity [36], and admission diagnosis of the patients.

The data analysis will firstly consist of a comparison between hospitals that have received the intervention and hospitals that have not yet received the intervention, according to the stepped wedge schedule. This will be done using multilevel linear regression and multilevel logistic regression analyses. In these analyses, we will adjust for temporal trends and for clustering within hospitals using generalised estimating equations.

Different organisational or system factors that might influence adherence to the intervention or might lead to differences between hospitals in delivered care will be analysed. These factors include hospital type (academic, teaching, general), size, location (urban or rural), and type of records used (paper versus electronic).

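### The unblinded ward supplies the records and the blinded nurse samples only from those supplied, so the primary outcome is not protected against supply that shifts with trial condition

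*Protocol article*

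**What the plan says.** All of this is in the Protocol article.

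- **Route of the records (Data collection).** The ward supplies them. "If a ward provides the research nurse with more than 10 records fitting the inclusion criteria, the nurse will take a random sample", and the set sampled is whatever was supplied: "the nurse will take a random sample from the available records". At 10 or fewer, no sampling is described.
- **Blinding (Data collection).** "The research nurses will be blinded for the trial condition of the hospitals and are not employed by the hospital" where they review. By contrast, "the hospitals and wards cannot be blinded to the trial condition".
- **Knowledge of the crossover date (Study design).** "Hospitals will each be informed of the start date of the intervention prior to the start of the trial".
- **Eligible pool (Research population).** Age 70 or older, a stay of at least 24 hours, and a time window: "Only records of patients still in hospital at the time of the record review and patients discharged in the previous week will be included".
- **What is read from the records (Outcomes and data analysis).** "The percentage of elderly patients that are indeed screened for the risk of delirium is the primary outcome of this study". The covariates are age, gender, living situation, comorbidity and admission diagnosis, with adjustment for temporal trends and for clustering within hospitals.
- **Limitations (Discussion).** These cover registration versus care, record quality, the nurse's presence, selection of hospitals by speed of response, and uncertain baseline implementation. How records are supplied is not among them.

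**The concern.** Blinding the research nurse protects the reading of a record. It does not protect the step before, in which records are put in front of the nurse. As described, that step belongs to a party that knows its trial condition and has known its start date since before the trial.

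The shift would have to coincide with crossover, and the Intervention section shows how it could. On gaining access, a ward has a kick-off meeting, its nurses receive e-mail reminders, and it gets a monthly overview of course use. Attention to delirium therefore rises just when the condition changes. Staff who are newly attentive might offer fuller files without any intent to mislead.

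If that happened, the shift would follow each hospital's own start date rather than the calendar. Adjustment for temporal trends would not separate it from the intervention effect. The listed covariates describe patients, so they would not remove selection made on screening status itself.

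**Working it through.** **1. The plan's own counts.** 18 hospitals × 2 wards × 10 records = 360 per month, and 360 × 11 months = 3,960. Both stated figures reproduce. The issue is how records enter this sample, not how many there are.

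**2. Apparent rate under differential supply.** Let p be the true percentage screened. Let r be the chance that an unscreened eligible record is supplied, relative to a screened one, in intervention months. Sampling at random from what was supplied, or taking all of it, leaves the supplied proportion unchanged in expectation:

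apparent rate = p / (p + (1 − p) × r)

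Take p = 0.40 (the baseline in Sampling), no true effect, and r = 1 in control months. The values of r are assumptions.

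| r | Calculation | Apparent rate | Bias (points) | Share of the planned 20 points |
|---|---|---|---|---|
| 1 | 0.4 / 1.00 | 40.0% | 0 | 0% |
| 0.9 | 0.4 / 0.94 | 42.6% | 2.6 | 13% |
| 0.8 | 0.4 / 0.88 | 45.5% | 5.5 | 27% |
| 0.5 | 0.4 / 0.70 | 57.1% | 17.1 | 86% |
| 0.444 | 0.4 / 0.667 | 60.0% | 20.0 | 100% |

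**3. Constant selection.** If the same r applied before and after access, with no true effect, both conditions would show the same apparent rate and the difference would be zero. Only a change in r at crossover creates a spurious effect.

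**4. A single ward-month, as an extreme.** Suppose 15 patients are eligible and 6 are screened (40%). If 5 unscreened records are not supplied, the nurse receives 10, of which 6 are screened (60%). There is no shortfall against the target of 10 and no random step.

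**5. Bias against sampling error.** This uses the Hussey–Hughes variance for a stepped wedge with I = 18 hospitals, T = 11 periods and 20 records per hospital-month. Assumptions: two steps of one hospital followed by eight of two, ICC 0.10, total variance 0.25, two-sided 5% test.

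- Between-hospital variance τ² = 0.10 × 0.25 = 0.025. Variance of a hospital-month mean σ² = 0.90 × 0.25 / 20 = 0.01125.
- From this layout: U = 91 intervention cells, W = 1,141 (sum of squared period totals), V = 589 (sum of squared hospital totals).
- Variance = Iσ²(σ² + Tτ²) / [(IU − W)σ² + (U² + ITU − TW − IV)τ²] = 0.05797 / (497 × 0.01125 + 3,146 × 0.025) = 0.05797 / 84.24 = 0.000688.
- Standard error = 0.0262, or about 2.6 points.

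With no true effect, the nominal 5% false-positive rate becomes about 16% at r = 0.9 (bias about one standard error) and about 55% at r = 0.8 (about two).

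**The case against.** **This is a condensed article.** Retrieval lists and reviewer instructions commonly sit in the full protocol, which may require every eligible record to be offered. That is a fair limit on certainty. But the article does state the sampling route, including where the random step applies and what it draws from, so the point concerns a stated method and not only a missing detail.

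**Wards are not said to choose.** A reader might infer that wards decide which patients are reviewed. The text says only that a ward provides records that fit the criteria, and those criteria are objective. A natural reading is that the ward supplies everyone who qualifies. This stands: ward discretion is not documented, only left unguarded.

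**Motive and mechanism.** A reader might also infer that ward staff know what the review measures; the article does not say so. To limit bias, hospitals get no information on their performance during the study (Discussion), which removes one incentive. Each hospital is its own control, so a steady wish to look good largely cancels. Many eligible patients are still on the ward when the nurse visits, which makes withholding harder to hide. All of this lowers the likelihood of bias. None of it covers a change in supply that follows the rise in attention at access.

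**Detectability.** A reader might conclude that no analysis could ever reveal the problem. That goes too far. Fewer than 10 records in small wards would be visible, shifts in collected patient characteristics could be examined, and hospital admission lists could later expose under-supply. These checks are partial: case 4 above leaves no shortfall, and covariates need not move when selection is on screening status.

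**Conclusion.** The point holds as a gap in protection, not as demonstrated bias. As written, an unblinded party supplies the records from which the primary outcome is read, and neither the nurse's blinding nor the random sample acts until after that step. The effect is biased only if supply changes with trial condition, and upwards if unscreened records become relatively less likely to be supplied after access.

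Under assumed relative supply chances from 0.9 to 0.5, the spurious gain is 2.6 to 17.1 points of the planned 20. Even the mild end roughly equals one standard error under an assumed ICC of 0.10. The article gives no figure for differential supply, so these sizes show sensitivity and are not a forecast. The text does not support saying that wards select patients, that staff know the purpose of the review, or that the problem could never be found. The change is worth making because it is cheap and removes the dependence on ward supply.

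**What to change.** Have the blinded research nurse draw the 10 records at random from a complete list of the ward's eligible patients: aged 70 or older, stay of at least 24 hours, in hospital at review or discharged in the previous week, with objectors removed. If there are 10 or fewer, take all. For each ward and month, log the numbers eligible, objected, sampled and not retrievable, and report them by trial condition.

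If wards already offer every eligible record, one sentence saying so, together with these counts, would settle the point.

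The cost is a patient list per ward per month, clearing it of patients or representatives who objected (Ethical approval), and a little more of the same nurse's time. The article does not say whether external nurses can obtain such a list, so that needs to be arranged with each hospital. The planned number of reviews, about 3,960, does not change.

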### Research population

Records of patients admitted to the participating wards will be included in the study if the patient is 70 years or older and if the length of stay at the time of the record review is at least 24 hours. Only records of patients still in hospital at the time of the record review and patients discharged in the previous week will be included. A total of approximately 3,960 patient records will be reviewed in the course of the study.

### Sampling

The power calculation for the part of the study focused on the effect of e-learning for nurses on provided care (*i.e*., screening for delirium risk) resulted in a power of 0.8, based on the following assumptions: 18 hospitals (36 wards); an improvement of delirium risk screening of 20% (from having 40% of the elderly patients screened to 60%) after the e-learning introduction; an alpha of 0.05; a total of 360 patient records for reviewing per month; an intracluster correlation coefficient (ICC) of 1.0.

For the aspect of the study focused on the effect of e-learning on knowledge, we expect a power of 0.99 assuming the study is conducted in 36 wards (18 hospitals), with an e-learning effect size of 1.00 [22], an alpha of 0.05, at least 30 nurses per ward, and an intraclass correlation of 0.20. When adjusting the effect size to 0.5, a power of at least 0.8 is still achieved.

### Outcomes and data analysis

In the Frail Elderly Project hospitals are advised to screen all elderly patients directly after admission for the risk of developing or the presence of delirium, falls, malnutrition, or physical impairment. The e-learning course educates nurses on screening for delirium. The percentage of elderly patients that are indeed screened for the risk of delirium is the primary outcome of this study. Secondary outcome measures include: the percentage of elderly patients with an increased risk of delirium that are observed with the Delirium Observation Screening scale; the percentage of elderly patients with (an increased risk of) delirium that receive care aimed to prevent or treat delirium; and the percentage of elderly patients that are diagnosed with delirium. Covariates that will be used in the analysis are: age, gender, living situation, comorbidity [36], and admission diagnosis of the patients.

The data analysis will firstly consist of a comparison between hospitals that have received the intervention and hospitals that have not yet received the intervention, according to the stepped wedge schedule. This will be done using multilevel linear regression and multilevel logistic regression analyses. In these analyses, we will adjust for temporal trends and for clustering within hospitals using generalised estimating equations.

Different organisational or system factors that might influence adherence to the intervention or might lead to differences between hospitals in delivered care will be analysed. These factors include hospital type (academic, teaching, general), size, location (urban or rural), and type of records used (paper versus electronic).

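### Two secondary outcomes are percentages of patients at increased risk; if that status comes from the screening the course is meant to raise, the comparison can be biased and can hide or reverse a benefit

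*Protocol article*

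**What the plan says.** The section Outcomes and data analysis names screening as the primary outcome: "The percentage of elderly patients that are indeed screened for the risk of delirium is the primary outcome of this study". It adds that "The e-learning course educates nurses on screening for delirium". Sampling plans for the screened share to rise from 40% to 60%.

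Two of the secondary outcomes are confined to a subset of patients. One is "the percentage of elderly patients with an increased risk of delirium that are observed with the Delirium Observation Screening scale". The other is "the percentage of elderly patients with (an increased risk of) delirium that receive care aimed to prevent or treat delirium". The remaining secondary outcome, the percentage diagnosed with delirium, uses all elderly patients.

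On where risk status comes from, Data collection states that "Monthly patient record reviews of patients 70 years or older will be the main source of data" and, under detection of risk, that "The Frail Elderly Project has provided hospitals with screening instruments to assess these risks". It also mentions two alternative instruments that hospitals use. Delirium itself enters the data as a physician's diagnosis. The article does not say how a reviewed patient is classified as being at increased risk for the two secondary outcomes. It describes no classification made by the research nurses independently of the ward's screening.

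The planned covariates are age, gender, living situation, comorbidity and admission diagnosis. The analysis adjusts for temporal trends and for clustering within hospitals.

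**The concern.** On the route the article describes, a patient becomes known to be at risk when the ward screens and records the result. Screening is the behaviour the course teaches. If recorded status sets the denominator, more patients enter it after the course than before, and those who enter may be observed or treated at a different rate from those already in it. Random allocation of start dates does not protect a comparison within a subset formed in this way.

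The care outcome has a second entry route, through delirium. That route depends on recorded diagnosis, itself a secondary outcome. The Background section cites studies in which 32% to 67% of cases were missed, so better recognition could change this part of the denominator too.

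The covariates describe patients, not why a ward screened one patient and not another. Adjustment for time and cluster does not deal with this selection either. The limitations in the Discussion cover registration, record quality, the presence of the research nurse and the choice of hospitals, but not this point.

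At stake are the later links of the hypothesis in the Background section: observing at-risk patients and taking preventive or curative measures. If risk status is taken from recorded screening, a course that succeeds on the primary outcome could appear to have no effect, or a harmful one, on these.

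**Working it through.** **The plan's own figures.** 18 hospitals × 20 records × 11 months = 3,960, as stated in Research population. 36 wards × 10 records = 360, matching "a total of 360 patient records for reviewing per month". The article gives no expected rate for either disputed outcome, so every DOS rate and at-risk share below is an assumption.

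**Illustration 1.** Assumptions: half of at-risk patients are obvious and half are not; screening stays at 80% in the obvious and rises from 20% to 60% in the others; once screened, 70% and 30% respectively are observed with the DOS in both periods; no unscreened patient is observed. Screening of at-risk patients then goes from 50% to 70%, the same 20-point gain as in Sampling.

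- Planned measure, before: (0.8×0.7 + 0.2×0.3)/(0.8 + 0.2) = 0.62/1.0 = 62%.
- Planned measure, after: (0.8×0.7 + 0.6×0.3)/(0.8 + 0.6) = 0.74/1.4 = 52.9%.
- All at-risk patients: 0.62/2 = 31% before and 0.74/2 = 37% after.

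The measure drops 9 points while observation rises 6. If unscreened patients were instead observed at the same 70% and 30%, true use would be (0.7 + 0.3)/2 = 50% in both periods. The planned measure would still fall from 62% to 53%.

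**Illustration 2, with the article's 40% to 60%.** Assume 50% at risk in every group. The recorded denominator grows from 360×0.4×0.5 = 72 to 360×0.6×0.5 = 108 per 360 records, so 36/108 = one third of it was absent before. Assume DOS use of 10% in unscreened at-risk patients and a rise from 60% to 65% in those always screened. With d the DOS rate in the newly screened (10% before they are screened):

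- Measured after = (72×0.65 + 36×d)/108; measured before = 60%.
- All at-risk before = 0.4×0.6 + 0.2×0.1 + 0.4×0.1 = 30%.
- All at-risk after = 0.4×0.65 + 0.2×d + 0.4×0.1.

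| d | Measured change (points) | Change in all at-risk patients (points) |
|---|---|---|
| 50% | 0.0 | +10 |
| 40% | −3.3 | +8 |
| 30% | −6.7 | +6 |
| 20% | −10.0 | +4 |

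With equal at-risk shares, the sign reverses when d is below the control rate minus twice the gain in the always-screened, here 60 − 2×5 = 50%. If the at-risk share is 60% in the always-screened and 40% in the others, the measured changes become +1.25, −1.25, −3.75 and −6.25 points against true changes of +9.2, +7.5, +5.8 and +4.2.

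**Boundary cases** (50% at risk throughout).

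- No DOS effect in anyone (always-screened 60%, newly screened 30% in both periods): measured after = (72×0.6 + 36×0.3)/108 = 50%, a change of −10 points against a truth of 0.
- Newly screened patients move from 10% to the same 60% as the always-screened: measured change 0, truth +10 (30% to 40%). The benefit is hidden, not reversed.
- DOS use equal in everyone and unrelated to screening: measured change 0, truth 0. There is no bias.

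**Check of the remedy.** In the d = 40% row, DOS use among all patients aged 70 or older goes from 0.5×30% = 15% to 0.5×38% = 19%, if patients not at risk are not observed. The sign is right. A numerator that also requires recorded risk does not work: with no DOS effect in anyone, it moves from 0.4×0.6 = 24% to 24% + 0.2×0.3 = 30% of at-risk patients.

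**The case against.** The strongest reply is that the source of risk status is inferred. The research nurses read nursing and medical records and collect demographic and clinical characteristics on every patient. Risk could be classified from these in the same way in both periods, and the problem would then largely disappear. A journal article may leave such an operational definition to the full protocol. This stands, and it makes the point conditional. It does not remove it, because recorded screening is the only route the article describes.

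A reader might infer that the control-period denominator holds mainly obvious cases. The article does not say so. It advises screening all elderly patients, and it admits that implementation may vary between hospitals, so a 40% average could come from some hospitals screening nearly everyone and others few. Clustering adjustment and the case-mix covariates may then reduce the shift. Selection on obviousness is not needed for a distortion, however: the case in which newly screened patients are observed exactly like the others still hides a 10-point gain.

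A reader might also treat the care outcome as affected in the same way as the DOS outcome. It is not. Diagnosed delirium admits patients without risk screening, which dilutes the dependence on screening but adds dependence on recognition. No figure is derived here for that outcome.

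Finally, the planned measures match the stated hypothesis about at-risk patients. That is a fair reason to keep reporting them, but not to rest the comparison of conditions on them.

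**Conclusion.** The point holds in conditional form. If recorded status defines who is at increased risk or has delirium, the denominators of two secondary outcomes are formed after the intervention, and the comparison can be biased. Under the assumed rates, the measured change in DOS use ranged from slightly positive to 10 points negative in scenarios where true use rose by 4 to 10 points.

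The stronger reading, that the comparison is necessarily biased or will change sign, is not supported. The article does not state how risk is determined, all DOS rates here are assumptions, and there is no bias if DOS use is unrelated to screening. The primary outcome and the percentage diagnosed use all elderly patients and do not have this denominator problem. The matter therefore deserves correction but does not threaten the main result.

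**What to change.** State how increased risk is determined for these outcomes. Then compare conditions on denominators that the course cannot change:

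- the percentage of all reviewed patients aged 70 or older with any recorded DOS observation, regardless of recorded risk status;
- the percentage of all reviewed patients aged 70 or older with recorded preventive or treatment care for delirium.

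Alternatively, define the at-risk group from admission characteristics already collected (such as age, comorbidity, living situation and admission diagnosis), by one rule applied alike in both periods.

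Do not require recorded risk in the DOS numerator, because that would credit the course for screening alone. Report the percentages among recorded at-risk patients as supportive, with a caveat on selection.

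The all-patient option changes outcome wording only and uses data already planned. Its cost is lower percentages that compare less directly with guideline indicators. The alternative also needs a classification rule written in advance.
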